**Methods:**

This is a 3-arm crossover randomized controlled trial (in-person DfPD vs online DfPD vs control) of UPGRADE-PD (Upbeating Greek Application of Dance in Parkinson’s Disease). The experimental period will be 10 months, including three 2-month interventional periods of two 60-minute dance classes per week for each group (in-person DfPD vs online DfPD) versus a control group (nonintervention group), and two 2-month washout periods between each group for 40 Greek patients with early- to midstage PD. Assessments will be performed face-to-face at baseline and at the end of each study period and will include quality of life, fatigue, depressive symptoms, stress, anxiety, sarcopenia, frailty, balance, cognitive functions, movement and nonmovement PD symptoms, and BMI. Safety, feasibility, and patient satisfaction for each dance intervention (in-person DfPD vs online DfPD) will be assessed as well.

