#### Intervention Description

A total of sixteen 60-minute DfPD classes will be conducted twice weekly for 8 weeks, both in-person and online, in a physiotherapy facility in Athens, Greece (in-person DfPD), and via Zoom platform (online DfPD; Zoom Communications, Inc), which will be free for the participants; the facility is licensed for the establishment and operation of physiotherapy activities. All the dance classes will be instructed by the main investigator (ME), who holds the approval to use DfPD for research reasons and is a licensed neurological physiotherapist, adapted physical educator, and dance educator. The exact structure and content of the program are described in Table 4. Participants will be instructed individually on how to use the Zoom platform before their program entry. Frequency and duration of the program are in accordance with past exercise and dance programs in patients with PD [30,45-48].

**Table 4 table4:** UPGRADE-PD (Upbeating Greek Application of Dance in Parkinson’s Disease) study’s DfPD structure and content.

Part (category) and track number		Type of activity		Type of exercise	Primal goals	Song title, album title (release date), composer

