**Patient satisfaction**
Willingness to continue the program after the intervention: a verbal statement for continuing the program after the end of the intervention in a 6-point Likert scale (0=I don’t know if I’d like to continue the program, 1=I don’t want to continue the program at all, 2=I don’t want to continue the program, 3=I might want to continue the program, 4=I want to continue the program, and 5=I want to continue the program very much) after the end of the program.Advantages and disadvantages of the program: there will be a total of 2 open questions: (1) Could you please list all the positive and negative points of the in-person Dance for Parkinson’s Disease (DfPD) intervention? and (2) Could you please list all the positive and negative points of the online DfPD intervention? These will be asked in a one-to-one interview of each participant by the principal investigator (ME) after the end of the program for the qualitative recording of advantages and disadvantages of each dance intervention from the patient’s perspective.

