### Data Collection and Management

All assessments will be conducted face-to-face by an independent investigator to eliminate possible detection bias, except of the Movement Disorder Society-Unified Parkinson’s Disease Rating Scale and Montreal Cognitive Assessment, which will be conducted face-to-face by specialized neurologists of the Eginition University Hospital Neurological Outpatient Clinic.

Participants are free to quit at any time if they wish to discontinue the study. In that case, reasons for withdrawal will be recorded, if this is possible. Participant’s enrollment will be followed by the research team’s assistance during the entire study period, including scheduling of data collection appointments, reminding of intervention’s appointments, and communicating the starting time of each research period.

Data, including consent forms, completed paper-based data files, and study notes, will be securely stored in the main investigator’s office, which will be locked. Raw data will be encrypted and stored digitally on a local computer with access rights to the main investigator. All original data will be archived for 5 years after the completion of the research and then destroyed, according to local regulations. All written data will be stored in a locked cabinet of the main investigator’s locked office for 5 years and then destroyed. Digital data will be stored on a password-protected local computer.

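### Willingness to continue is coded with undecided participants below outright refusers and is not asked by format, and the open satisfaction questions are put by the class instructor

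*Protocol article*

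**What the plan says.** Patient satisfaction is a key secondary outcome (Protocol article, Textbox 3). It has two parts.

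- **Willingness to continue.** This is "a verbal statement for continuing the program after the end of the intervention in a 6-point Likert scale". The scale begins "0=I don’t know if I’d like to continue the program, 1=I don’t want to continue the program at all" and ends "5=I want to continue the program very much) after the end of the program". The item names neither the in-person nor the online format.
- **Open questions.** There are two, one on the good and bad points of each format. "These will be asked in a one-to-one interview of each participant by the principal investigator".

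Four other places bear on this:

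- The abstract (Methods) states that "patient satisfaction for each dance intervention (in-person DfPD vs online DfPD) will be assessed as well".
- Table 3 lists patient satisfaction under Assessments, with one tick, at the last visit (T5, week 45).
- Intervention Description says "All the dance classes will be instructed by the main investigator". The document's initials identify this person as the principal investigator who holds the interview.
- Data Collection and Management says "All assessments will be conducted face-to-face by an independent investigator to eliminate possible detection bias". The only exceptions it names are the MDS-UPDRS and the MoCA.

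**The concern.** There are three separate faults.

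1. **Order.** A scale presented as one six-point Likert scale should be ordered throughout. Here the don't-know answer lies below the strongest refusal. If the codes are averaged or ranked, an undecided participant lowers the score more than one who refuses outright.
2. **Object rated.** The only numerical satisfaction measure asks about the program as a whole. A single undivided rating from someone who has received both formats gives no within-participant contrast between in-person and online.
3. **Interviewer.** Participants are asked face to face to name negative points to the person who taught them. That invites courteous answers. It also departs from the document's general rule that someone independent makes the assessments.

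At stake is how a key secondary outcome is interpreted: the level of willingness, the promised result for each format, and the candour of the qualitative answers. The primary PDQ-8 analysis is not affected.

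**Working it through.** The plan gives no sample size, power or target for satisfaction, so there is no figure of its own to reproduce. The check is arithmetic on the codes and a comparison of sections.

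**Coding.** Inputs from Textbox 3: don't know = 0, outright refusal = 1, top category = 5. Let m be the mean on codes 1 to 5 among those with an opinion, and d the share answering don't know. Averaging codes 0 to 5 gives (1 − d) × m, a fall of d × m. The document supplies neither m nor d, so both are assumed. Two values of m are used: 4.5, and 3.85, which follows from assumed shares of 5%, 5%, 20%, 40% and 30% on codes 1 to 5 (0.05 + 0.10 + 0.60 + 1.60 + 1.50).

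| d | m = 4.5: mean (fall) | m = 3.85: mean (fall) |
|---|---|---|
| 5% | 4.275 (0.225) | 3.66 (0.19) |
| 10% | 4.05 (0.45) | 3.465 (0.385) |
| 20% | 3.60 (0.90) | 3.08 (0.77) |

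The order fault shows directly in two assumed sets of 40 answers:

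- 20 participants at code 4 and 20 undecided: (20 × 4 + 20 × 0) / 40 = 2.0.
- 20 participants at code 4 and 20 outright refusers: (20 × 4 + 20 × 1) / 40 = 2.5.

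The group containing refusers scores higher than the group containing undecided participants.

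**Format.** The abstract promises satisfaction for each format. The willingness item does not name a format, and Table 3 schedules satisfaction once. Elsewhere in Textbox 3 the authors do name formats: adherence and attrition are assessed for each dance intervention, and each open question names one format. That the willingness item is a single undivided rating is an inference from this contrast and the single tick; the text does not say so outright.

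**Recall.** Periods end at weeks 9, 27 and 45 (Table 3), so a judgement at week 45 comes 45 − 9 = 36, 45 − 27 = 18 or 45 − 45 = 0 weeks after a format ended. From Table 1:

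| Sequence | In-person lag (weeks) | Online lag (weeks) | In-person minus online |
|---|---|---|---|
| ABC | 36 | 18 | +18 |
| BCA | 0 | 36 | −36 |
| CAB | 18 | 0 | +18 |
| ACB | 36 | 0 | +36 |
| BAC | 18 | 36 | −18 |
| CBA | 0 | 18 | −18 |

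Each format has each lag in two of the six sequences, and the differences sum to 0. Every participant recalls the two formats at unequal distances, but across sequences the lags balance. With 40 participants the balance is approximate, because 40 / 6 is not a whole number.

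**Interviewer.** Set side by side, Data Collection and Management assigns every assessment except two scales to an independent person, Table 3 counts satisfaction as an assessment, and Textbox 3 gives the open questions to the instructor. Textbox 2 states the rule more narrowly: the independent researcher performs the assessments before and after each research period, while the main researcher handles all communication with patients. Textbox 3 does not say who takes the willingness rating.

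**The case against.** A reader might infer that the satisfaction data cannot compare the two formats fairly. The documents do not support that, for four reasons.

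- **Instructor courtesy.** One person teaches both formats, so courtesy acts on both. It may raise the general level of praise, but nothing shows that it favours one format. The open questions also ask for negative points on each format.
- **Recall lag.** It is balanced across sequences by design, so it is a source of noise and not a between-format bias. Asking at the end, when participants have tried both formats, is defensible; a participant at T1 has tried at most one. Period-end timing is a trade-off.
- **Coding.** It does harm only if code 0 is averaged or ranked. Statistical Analysis promises a method suited to the type of end point, and the unseen analysis plan may settle the matter. The music-preference item also uses 0 for not knowing, and Table 6 reports only the number and percentage in the top category. Reported that way, code 0 would distort no mean.
- **Single tick.** Adherence and attrition also have one tick at T5, although they are assessed for each intervention. The tick alone does not prove an undivided rating.

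Textbox 2's narrower wording also softens the conflict over the assessor: the interview can be read as an end-of-program qualitative record outside the before-and-after assessments.

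These arguments remove the claim of unfairness between formats. They do not put the scale in order or add a format to the willingness item. Nor do they remove the risk to candour, or the broader wording in Data Collection and Management.

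**Conclusion.** The point holds as three limited faults.

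1. The scale as labelled is not ordered. If codes 0 to 5 are averaged, the mean falls by d × m: between 0.19 and 0.90 points for 5% to 20% undecided under the two assumed means. If the answers are reported only as category percentages, the distortion is nil. The coding does not by itself favour a format.
2. Followed as written, the willingness item does not deliver the satisfaction for each format that the abstract promises. This rests on the item's wording and the single scheduled visit. The open questions meet the promise in part, qualitatively.
3. Having the instructor ask the open questions is a risk to candour for both formats. Its size cannot be derived from the documents. Textbox 3 and Data Collection and Management need to be reconciled, with Textbox 2 taken into account.

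The faults weaken the satisfaction results but do not show a biased in-person versus online comparison.

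**What to change.** - **Coding.** Analyse willingness on the ordered codes 1 to 5 and report don't know as a separate category with its count. Results says analysis starts only after the last participant has left the study, so this remains possible for ratings already collected.
- **Format.** Ask the item separately for in-person and online, at T5 at the latest, and compare within participant. Asking at the end of each format's period would shorten recall, but some participants would then answer before trying the other format.
- **Collection.** Have the existing independent assessor, or a self-completed form, collect both the rating and the open questions. State who takes the rating, and reconcile Textbox 3 with Data Collection and Management and Textbox 2.
- **Where ratings were taken only once.** Recode 0 as a separate category and state in the report that willingness was not rated by format.

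The cost is one extra item at an existing visit and a coding change. No new staff are needed, because an independent assessor is already part of the design.

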#### Secondary Outcomes

The other expected secondary outcomes are outlined in Textbox 4.

Other secondary outcomes.
**Fatigue**
Parkinson Fatigue Scale-16 (PFS-16): fatigue will be assessed before and after each research period by the change in total score of the Greek version [101] of PFS-16 [102], which is a 1- to 5-point scale with a higher score indicating more fatigue.Modified Fatigue Impact Scale: fatigue will be also assessed before and after each period by the change in total score of the Greek version [103] of the Modified Fatigue Impact Scale [104], which is validated in the population with Parkinson disease (PD) [105] 0- to 84-point scale, with a higher score indicating more fatigue.
**Depressive symptoms**
Depressive symptoms will be assessed before and after each research period by the change in total score of the Greek version [106,107] of the depression subscale score of Depression, Anxiety, and Stress Scale-21 (DASS-21) [108], which is a validated in the population with PD [109] 0-to-42-point scale with 0 to 9 indicating no symptomatology, 10 to 12 indicating mild symptomatology, 13 to 20 indicating moderate symptomatology, 21 to 27 severe symptomatology, and 28 to 42 extremely severe symptomatology.
**Stress**
Stress will be assessed before and after each research period by the change in total score of the Greek version [106,107] of the stress subscale score of DASS-21 [108], which is validated in the population with PD [109] 0-to-42-point scale, with 0 to 10 indicating no stress, 11 to 18 indicating mild stress, 19 to 26 indicating moderate stress, 27 to 34 severe stress, and 35 to 42 extremely severe stress.
**Anxiety**
Anxiety will be assessed before and after each research period by the change in total score of the Greek version [106,107] of the anxiety subscale score of DASS-21 [108], which is validated in the population with PD [109] 0- to 42-point scale, with 0 to 6 indicating no anxiety, 7 to 9 indicating mild anxiety, 10 to 14 indicating moderate anxiety, 15 to 19 severe anxiety, and 20 to 42 extremely severe anxiety.
**Sarcopenia**
Sarcopenia risk will be assessed before and after each research period by the change of total score of the Greek version [110] of Strength, Assistance in walking, Rise from a chair, Climb stairs, and Falls Scale [111], which is a 0 to 10 self-reporting screening tool of five 0- to 2-point components (strength, assistance walking, rise from a chair, climb stairs, and number of falls) with 0 to 3 indicating no risk for sarcopenia, and ≥4 indicating risk of sarcopenia.Sarcopenia status will be assessed before and after each research period by the change of European Working Group on Sarcopenia in Older People criteria [112], as has been previously assessed in the PD population [113]. According to the European Working Group on Sarcopenia in Older People, sarcopenia is (1) probable in an individual with low muscle strength (hand grip strength [HGS] for men: <27 kg and women: <16 kg), (2) confirmed in an individual with the above criteria combined with low muscle quantity (appendicular skeletal muscle mass index for men: <7 kg/m^2^ and women: <5.5 kg/m^2^), and (3) severe in an individual with the 2 above criteria combined with low physical performance (4 m usual walking speed test≤0.8 m/s). HGS will be assessed by a calibrated digital handheld dynamometer, appendicular skeletal muscle mass index by a bioelectrical impedance analysis equipment, and physical performance by the4-m usual walking speed test.

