While physical exercise seems to induce neuroplasticity in people with PD [5], dance has been associated with favorable changes in the corticospinal tract, the corpus callosum, the superior longitudinal fasciculus, the dorsolateral prefrontal cortex, the bilateral putamen, the mirror neuron system, and sensorimotor pathways of healthy dancers [9,19]. Following the aforementioned effects of dance in neuroplasticity, dance in PD seems to enhance psychological flexibility (thus the person tends to adapt to environmental changes more efficiently) and creative self-efficacy (thus the person tends to think creatively and execute these thoughts) [20]. Dance, compared to other types of exercise, improves PD symptoms, such as balance, functional mobility, and cognition [21-24]. Moreover, dance is a substantial motivational means of exercise for patients with PD, enhancing their adherence rates to exercise programs [25,26], as well as a safe, feasible, and enjoyable intervention for patients with early- to midstage PD [27], even when the classes are remotely conducted [28].

Dance for Parkinson’s Disease (DfPD) is a structured dance program under appropriate care and supervision especially designed for people with PD, which integrates different dance genres [29]. Various studies have already described the content of the DfPD class that was followed [30-32]. To our knowledge, there is no published study investigating the effect of DfPD on the frailty and sarcopenia experienced by patients with PD. In addition, no randomized controlled trial to date has been conducted to investigate either the effect of this program on any clinical parameter in Greek patients with PD or the possible differential effect of in-person versus online DfPD. Furthermore, there is no published protocol of any patient-centered or culturally tailored dance intervention for the PD population showing the exact methodology that was followed and the content of the dance intervention. This study aims to fill the above gaps by publishing all the aforementioned data of our research protocol.

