**Frailty**
Frailty will be assessed before and after each research period according to the most often used frailty scale in PD [4] frailty phenotype (FP) status [114], in which 5 criteria have to be assessed: (1) unintentional weight loss >5 kg the last year, (2) weakness (HSG for men: <27 kg and women: <16 kg), (3) slow walking speed (10-m usual walking speed test ≤0.8 m/s), (4) exhaustion (PFS-16 total score ≥3, which indicates moderate to severe fatigue), and low levels of physical activity (a total score <600 MET/min/week^-1^ indicates inactivity in the Greek version of International Physical Activity Questionnaire-Short Form [115]). The FP score ranges from 0 to 5 (1 point for each criterion; 0: best score to 5: worst score), and defines as frail an individual with a score of ≥3, as prefrail an individual with a score of 1 to 2, and as nonfrail or robust an individual with a score of 0.

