### Sample Size

A prospective, nonrandomized, uncontrolled, open-label pilot study has already been conducted in a Greek population of 16 patients with early- to midstage PD, showing that in-person DfPD is safe and feasible, and can improve QoL, as well as several movement and nonmovement PD symptoms [45]. According to the results of the above pilot clinical trial for our primary outcome (QoL), the Cohen equations for sample size calculation [124], and considering the power of the study equal to 80% and the level of statistical significance of the controls equal to the conventional limit of statistical significance (α=.05), a power analysis was applied with the a priori formula for the *F* test statistical control through analysis of variance with repeated measures using G*Power software (version 3.1) [125].

Taking in consideration that the number of experimental groups will be 3, the number of repeated measurements for each participant will be 6, and the average correlation coefficient between repeated measurements will be 0.64, it was estimated that for this study, which has a 1:1:1:1:1:1 distribution ratio of participants to the groups, at least 6 participants are required in each group (18 in total). On the basis of the equations that adjust the sample size to the expected dropout rate [126], which is expected to be up to the 15% acceptable value, based on the Physiotherapy Evidence Database Scale [99], the minimum sample size required to achieve the study’s primary end point (QoL) is 21 participants.

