### Statistical Analysis

The primary analysis will evaluate the between group differences in total score of the Greek version of Parkinson’s Disease Questionnaire-8 after each research period. Mean (SD) or summary statistics appropriate to the distribution of the QoL total score will be reported by study group (in-person DfPD vs online DfPD vs control). Study groups will be compared in terms of QoL using mixed model repeated measures considering the correlated data from the same patient [128]. Mixed model repeated measures are robust in small sample size studies; thus, a decreased risk of type II errors occurs [129]. For all secondary end points, summary statistics will be tabulated by study group, and study groups will be compared with a statistical method appropriate to the type of the end point (eg, continuous and categorical end point). Bonferroni correction will be used to account for multiple comparisons of secondary outcomes.

A secondary analysis of the primary end point will adjust for those prerandomization variables which might reasonably be expected to be predictive of favorable QoL total score. Any deviations from the protocol will be recorded and agreed by the investigators. Missing data will not be imputed neither for primary nor secondary analyses, and no interim analyses will be conducted in this study. All the *P* values are 2-sided at an α level of .05. Analyses will be conducted with SPSS (version 20.0; IBM Corp) and R (version 4.4.1; R Foundation for Statistical Computing).

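### EWGSOP2 status and frailty phenotype status are blunt measures of an 8-week effect, and the one-year weight-loss item cannot be tied to one crossover period; the continuous values already collected should be analysed

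*Protocol article*

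**What the plan says.** Textbox 4 (Other secondary outcomes) names two sarcopenia outcomes. The first is the change in SARC-F total score, a 0-10 self-report screen. The second is a classification: "Sarcopenia status will be assessed before and after each research period by the change of European Working Group on Sarcopenia in Older People criteria". Its levels are nested. Low grip strength (under 27 kg for men, under 16 kg for women) gives probable sarcopenia. Adding low appendicular muscle mass index gives confirmed, and adding a 4-m walking speed of 0.8 m/s or less gives severe. The instruments are specified, for example: "HGS will be assessed by a calibrated digital handheld dynamometer".

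Frailty is assessed by phenotype status from five yes/no criteria, each scoring one point, with a 0-5 score and robust, prefrail and frail classes. One criterion is "unintentional weight loss >5 kg the last year". The other four (grip, 10-m walking speed, PFS-16, physical activity) carry no one-year look-back.

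Table 3 schedules EWGSOP2, frailty phenotype and BMI at all six assessments (weeks 0, 9, 18, 27, 36 and 45). Under Statistical Analysis, the method for secondary end points follows the type of end point, these end points are Bonferroni-corrected, and P "values are 2-sided at an α level of .05". The Background gives one reason for the trial as "there is no published study investigating the effect of DfPD on the frailty and sarcopenia experienced by patients with PD", among other gaps such as in-person versus online delivery.

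**The concern.** A classification moves only when someone crosses a cut-off. Because EWGSOP2 is nested on grip, a man at 27 kg or more, or a woman at 16 kg or more, has no sarcopenia status whatever happens to muscle mass or walking speed. Eligibility (Hoehn and Yahr 0-2.5, no comorbidity seriously affecting mobility) makes it likely that few participants start below the grip cut-off, although the article gives no baseline distribution. Real changes in kg, kg/m² or m/s could then leave the status table almost unchanged.

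The frailty problem is structural. A crossover attributes each outcome to the treatment of its period and relies on washouts for separation. A criterion that looks back a year is longer than the trial itself, so no washout in this design can clear it. At stake is the ability to answer one of the questions the trial was set up to answer.

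**Working it through.** **The plan's own figure.** No sample size or power is stated for sarcopenia or frailty. The only figure is 21 participants for QoL, built from 18 with 15% dropout: 18 × 1.15 = 20.7, or 18 / 0.85 = 21.2. It reproduces to within one participant and has no bearing on these outcomes.

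**Information kept by one cut-off.** For a normal measure with share p below the cut-off z, efficiency relative to the continuous value is φ(z)² / [p(1−p)]. Completers are taken as 40 × 0.85 = 34. The values of p are assumptions.

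| p below cut-off | φ(z) | Efficiency | × 34 completers |
|---|---|---|---|
| 0.50 | 0.3989 | 0.637 | 21.6 |
| 0.20 | 0.2800 | 0.490 | 16.7 |
| 0.10 | 0.1755 | 0.342 | 11.6 |

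**Power on the same footing.** Model: bivariate normal, two conditions compared within patient, n = 40, two-sided 0.05, correlation 0.64 (borrowed from the QoL calculation), and an assumed true shift of 0.5 SD. A paired t test on the value is set against an exact McNemar test on one cut-off.

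| p below cut-off | Expected to improve / worsen | McNemar power | Paired t power |
|---|---|---|---|
| 0.05 | 1.7 / 0.3 | 0.5% | 95% |
| 0.10 | 3.2 / 0.7 | 5.5% | 95% |
| 0.20 | 5.7 / 1.3 | 23% | 95% |
| 0.30 | 7.6 / 1.8 | 37% | 95% |
| 0.50 | 10.0 / 2.4 | 50% | 95% |

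With a 0.3 SD shift, power is 59% for the continuous value and 0.3% to 19% for the cut-off. With n = 34 and 0.5 SD it is 92% against 0.2% to 42%. The highest cut-off power found was 72% (p = 0.50, 0.5 SD, correlation 0.9), where continuous power is about 100%.

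**The one-year window.** Look-back at week w runs from w − 52 to w.

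| Assessment | Window (weeks) | Trial time covered |
|---|---|---|
| T1, week 9 | −43 to 9 | period 1; 43 of 52 weeks precede the trial |
| T3, week 27 | −25 to 27 | periods 1 and 2, washout 1 |
| T5, week 45 | −7 to 45 | all three periods, both washouts |

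An 8-week intervention fills 8/52 = 15% of the window, and a 9-week interval between assessments fills 9/52 = 17%.

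**Does subtracting the period baseline help?** The T4 window is −16 to 36 and the T5 window is −7 to 45. They share weeks −7 to 36, which is 43 of 52 weeks. The change from T4 to T5 therefore adds weeks 36 to 45 and drops weeks −16 to −7, before randomization. Because the item is a threshold on cumulative loss, the shared weeks do not simply cancel:
- A loss in period 1 that stops short of 5 kg can be completed by a smaller loss in period 3, and the point is then scored in period 3.
- Someone who crossed 5 kg in period 1 may already hold the point at later baselines and cannot gain it again.
- A point can disappear because an old loss ages out of the window.

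**The case against.** There is a fair case against each half, and part of it stands.

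- *Sarcopenia is not judged by status alone.* Correct. SARC-F total score is numeric and is assessed at every visit. It is a self-report risk screen, however, and does not replace measured grip, muscle mass or speed.
- *The outcomes can move.* Correct. A reader might infer that status cannot register an 8-week effect, but the documents do not support that: every EWGSOP2 component and four of the five frailty criteria can cross a cut-off within a period, and cut-off power reached 72% in the most favourable setting.
- *A 0-5 frailty score exists.* Correct, and the choice between score and class may be settled in a fuller plan. The one-year item sits in both, so that part of the point does not depend on the choice.
- *Paired baselines share most of the weight history.* Correct, at 43 of 52 weeks, but a threshold on a running total does not cancel as a difference of values would.
- *The arithmetic models one normal variable cut once.* Correct. EWGSOP2 has nested levels from three measures, and the frailty phenotype is a five-item count. The figures show direction and rough scale, not the power of the actual analysis.
- *These are secondary outcomes.* Correct. The sample size addresses QoL only, and frailty and sarcopenia are one of several stated gaps. That a null result would be reported as no effect of dance is also only an inference; the article does not say so.

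**Conclusion.** The point holds as a matter of sensitivity and attribution. The threshold outcomes are poorly sensitive to an 8-week effect while better-suited continuous values are collected and left unnamed. For a single cut-off, about 34% to 64% of the information is kept at an assumed 10% to 50% below it, and the continuous value had more power in every setting tried. Those sizes rest on assumed prevalence, shift and correlation, because the article gives no baseline distributions.

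The weight-loss point needs no such assumption. It follows from the visit weeks and the criterion's wording: one of five frailty criteria cannot be assigned to a single period, and baseline subtraction mends this only in part. It concerns frailty only, not sarcopenia. The primary analysis is unaffected. The change is worth making because it is cheap and bears on a stated aim of the trial.

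**What to change.** - Name grip strength (kg), appendicular muscle mass index (kg/m²) and walking speed (m/s) as continuous secondary outcomes, analysed in the same mixed model as QoL. State which walking test is meant, since sarcopenia uses a 4-m test and frailty a 10-m test.
- Report EWGSOP2 status descriptively by group and assessment. Leave SARC-F as it is.
- For frailty, state whether score or class is compared. For period comparisons, add a sensitivity analysis on the 0-4 score without the one-year item, beside the published five-criterion version. Report weight change from the period baseline, using the weights taken for BMI.
- Record the change before analysis begins; otherwise label these analyses post hoc. The article says analysis starts after the last participant leaves the study.

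Cost: no new data. Three continuous tests in place of one status test add two net tests under Bonferroni. The article does not give the number of tests. If it were 12, moving to 14 would lower continuous power from 75% to 73% in the setting above (n = 40, 0.5 SD, correlation 0.64), against at most 16% for a cut-off at 12 tests. The 0-4 frailty score is not the published instrument, so both versions must be shown.
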